#### The self-monitoring, feedback, and evolution module

Only the design and key features of the module will be discussed here, details on the instruments used for self-monitoring are described in the “Outcomes” section of the paper.

#### Self-monitoring

The self-monitoring module serves two relevant functions, detailed below.

The first function is to assist users in self-monitoring their own eating and physical activity patterns, a proven predictor of weight-loss and weight management [42]. SIGMA includes self-monitoring components aimed at monitoring dietary intake and physical activity, enabling users to plan a meal/menu and physical exercise in advance and offering personalized tips (i.e., psycho-educational content) and feedback regarding eating and physical activity styles.

Aside from planning, the monitoring of physical activity is aided by an embedded *pedometer*. The decision to incorporate a pedometer was informed by the fact that it has been reliably associated with significant increases in physical activity and significant decreases in BMI ([43]). The pedometer will monitor and compare the user’s daily performance with a daily suggested target and will provide feedback and healthy habit points accordingly. As such, a norm of between 5000 and 7499 steps/day is considered low active, 7500 to 9999 steps/day is somewhat active, and 10,000 or more steps/day is considered an active lifestyle [44]).

The second function, drawing on the cognitive-behavioral principles, is to monitor how well the participants apply the CBT principles of the SIGMA game to real-life situations. Hence, a special feature of the monitoring module is the *ABC diary* that focuses on understanding the *A*ntecedents and *C*onsequences of maladaptive *B*eliefs regarding food, weight or the ability to maintain the diet. This should aid the users in noticing and challenging their maladaptive patterns without relying on a therapist for weight management.

Regarding the consequences of eating behaviors, users will be enabled to monitor their levels of reported satiety after a meal, as well as their emotional reactions after eating, such as guilt or satisfaction. Lower levels of satiety and negative emotional reactions after eating may predict a relapse and it is important for the app to offer alternative ways of thinking in tempting or adverse situations. This should help alleviate urges to eat outside planned meals or prevent feelings of guilt when it happens.

#### Feedback and evolution

The first 2 weeks of SIGMA usage focus on calibrating the SIGMA intervention through a baseline evaluation of the users’ behavioral and cognitive patterns (e.g., more emotional eating content for individuals with emotional eating issues). Following the initial baseline evaluation, the SIGMA app will produce a report identifying the users’ vulnerabilities that will also serve as a starting point for customizing the intervention. For instance, if the evaluation reveals that a user is more likely to succumb to dietary temptations in the evening, the app will send more tips and motivational messages at that specific time. Moreover, the feedback report is designed to be intuitive; for instance, the user’s points and the number of steps on the pedometer are delivered through a meaningful interpretation of the progress (e.g., “This week, you have accumulated X out of Y possible points and the total number of steps taken is equivalent to the distance from A to B”).

Feedback plays an important role in the serious game module, as each progress or failure is followed by feedback along with a detailed statement explaining why the specific choice made during SIGMAe or SIGMAi was erroneous. SIGMA will also provide feedback, in the form of charts, regarding the cognitive, behavioral, and emotional indexes of progress as compared to the user’s baseline level. Feedback on user’s progress (i.e., number of accumulated points, mastery level) will be based on objective assessments. These assessments are represented by both the healthy choices made during the SIGMAi trials, as well as the healthy cognitive and behavioral coping choices made during the SIGMAe trials.

Moreover, the SIGMA app uses a complex and novel scoring system that allows SIGMAe and SIGMAi points to be supplemented by points earned during outdoor activities with the help of a pedometer. As such, additional points are earned depending on the level of activity (i.e., daily step count) the user is willing to make. We do not want to encourage a fixation on other outcomes such as calorie counting or daily weighing [45]. However, we have embedded a calorie counter in the SIGMA app. Overall, all the earned points help the user reach a higher mastery level.

### The SIGMA randomized controlled trial (RCT)

The SIGMA trial is set to be a randomized, placebo-controlled trial that is nationally funded through a research grant. Throughout this trial, the SIGMA intervention will be contrasted against a specific form of placebo, also known as an *attention placebo control condition*. An attention placebo control refers to a condition that mimics an intervention but does not address the proposed mechanisms of change. Participants allocated to the attention placebo control condition will have full access to a modified version of the SIGMA app, which includes all the SIGMA modules except for the gamified intervention module. This control condition is highly suitable to investigate the active ingredients of an intervention, as in our case. Furthermore, this type of control arm is considered a highly valid control condition for RCT’s [46]. Ethical approval for this study was sought and received from the Ethics Committee of the Babeș-Bolyai University (Cluj-Napoca, Romania) and from the Ethics Committee of the University of Bucharest (Bucharest, Romania).

The SIGMA trial will have 2-week calibration point followed by a 2-month intervention and a 3-month follow-up. The schedule of the trial is presented Fig. 4.

**Fig. 4 Fig4:**
[figure not shown]
Recommendations for Interventional Trials (SPIRIT) figure – schedule of enrolment, intervention, and assessments

The primary aim is to determine whether the SIGMA intervention is more effective than the attention placebo control condition in reducing maladaptive behaviors and cognitive styles, as well as in increasing their adaptive/functional counterparts. Our working hypothesis is that the SIGMA intervention will be significantly more effective in promoting change in maladaptive behaviors and cognitive styles, decreasing the maladaptive counterparts and increasing adaptive food-related behavioral and cognitive styles of response. Significant differences favoring the SIGMA intervention are to be expected in an evidence-based intervention, as more extensive use of theory in eHealth interventions is associated with an increase in effect size [47]. This change is expected to be maintained at follow-up.

The secondary aim is to determine whether the SIGMA intervention is more effective than the attention placebo control condition in reducing weight (e.g., kg, BMI), physical activity-related parameters (i.e., increase the number of steps per day), and general mood. The hypothesis is that the SIGMA intervention will be significantly more effective in prompting change in weight-related, physical activity patterns and even general mood relative to the attention placebo control group. This change is expected to be maintained at follow-up.

### Participants

#### Inclusion and exclusion criteria

Participants will be (1) young overweight adults (25 ≤ BMI ≤ 29.9), (2) aged between 18 and 35 years old, and with (3) maladaptive eating habits in the range of urgent food cravings, emotional eating or binge-eating patterns that do not meet the criteria for clinical eating disorders. Eligible participants will also have to own an Android-compatible smartphone that is able to connect to the Internet.

Volunteers will be excluded from the SIGMA trial in the following cases: (a) presence of any medical condition incompatible with physical/dietary recommendations (including pregnancy and type 2 diabetes); (b) presence of an eating disorder; (c) use of appetite-suppressing medication and/or current enrollment in other weight management programs; (d) current depression or any form of psychotic disorder; and (e) lack of access to an Android-compatible smartphone.

#### Recruitment

Potential participants will be recruited using multiple avenues of communication. Posters describing the intervention and the invitation to take part in the study will be posted in universities around the country. The electronic version of these posters will be distributed around the Internet with a special focus on weight-related forums, Facebook groups, and websites.

Emails describing the purpose of the intervention and an invitation to collaborate will be sent to entities concerned with curbing overweight/obesity rates. These are foundations or associations that are actively engaged in promoting healthy lifestyles by informing the general public about weight-related issues (e.g., Wings Foundation, The Association for Supporting Patients with Obesity, The Romanian Society for the Study of Obesity, etc.).

#### Sample size

In order to detect a medium effect size (i.e., Cohen’s *d* = 0.50), with a *p* ≤ 0.05 and 80% power, we would need a total of 74 participants, 37 participants per arm (calculated using G*Power, [48]). Assuming that up to 40% of participants will drop out of the intervention [16], a total of 104 participants will be needed (52 participants per trial arm) in order to detect the aforementioned effect size. The 40% percentage dropout rate represents the worst-case scenario as a high dropout rate can be sometimes expected in mHealth or eHealth studies [16].

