Maladaptive behaviors and cognitive styles can be best assessed and altered in their ecological environment. A potential avenue towards achieving this is the delivery of interventions through smartphone apps (i.e., mHealth interventions). These interventions are particularly relevant for the young adult population (i.e., 18 to 35 years old) for two main reasons. Firstly, young adults (i.e., 18 to 35 years old) are particularly susceptible to becoming overweight or obese (e.g., [12]). Moreover, weight gain during this life-stage is not only a marker of obesity but also for developing chronic disease risk factors (e.g., high blood pressure; [13]). Secondly, young adults are the most likely age group to own and constantly interact with smartphones. As many as 100% of young adults in developed countries own smartphones, with constantly increasing rates in developing countries as well [14, 15]. Therefore, the increased usage of mobile phones among the young adult population and the health consequences associated with early-life weight gain provide the motivation for delivering weight management interventions (i.e., mHealth) on a large scale and in an ecological manner.

Mobile or mHealth interventions for weight management have demonstrated promising results across various studies [16]. However, they face two important limitations, as argued below.

The first limitation is that most studies report up to a 50% dropout rate in the use of existing mHealth and eHealth applications (i.e., electronic/technologically mediated apps), which makes them subject to short-term use only [17]. A potential solution for long-term use would be to increase the interactivity and attraction of current mHealth interventions via gamification. Gamification refers to the employment of game-like components (e.g., challenges, storylines) in non-game contexts such as psychological interventions [18]. Although research on the topic remains in its initial stages, current evidence suggests that gamification can have a positive impact on motivation and health behaviors [19] and, most importantly, it promotes long-term treatment adherence [18, 20, 21].

A second limitation of existing m/eHealth interventions is that currently there is no available application or scientific trial targeting maladaptive eating habits despite their high prevalence in overweight individuals [22]. Hence, new portable, evidence-based, integrated, and interactive applications for weight management are needed.

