### Data analysis

To test the efficacy of the SIGMA intervention against the attention placebo control group a 2 (group: SIGMA intervention group versus attention placebo group) × 3 (time: pre vs. post vs. follow-up) general linear mixed model will be used with regard to the primary and secondary outcomes. Separate analyses will be performed for the “intent-to-treat” and the completer sample. The intent-to-treat principle will be employed [58] with the last observation carried forward method. The Bonferroni-Holm correction will be used to adjust for multiple comparisons. Overall, with a sample of at least 74 participants, the trial will be powered to identify at least a medium effect size (i.e., Cohen’s *d* = 0.50).

App usage data and user activity will be inspected by contrasting; for example, the participants’ self-reported activity with their actual app usage as recorded in the database. This will inform us about any impediments to user adherence, as well as particular usage patterns.

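### The 40% dropout allowance multiplies by 1.40 instead of dividing by 0.60, so 104 randomised leaves about 62 completers, not the required 74

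*Protocol article*

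**What the plan says.** The Sample size section takes a standardised difference of 0.50, a 5% significance level and power of 80%, and concludes: "we would need a total of 74 participants, 37 participants per arm". It then adjusts for attrition: "Assuming that up to 40% of participants will drop out of the intervention [16], a total of 104 participants will be needed", split as 52 per arm, and says that this number serves to detect the same effect size. On the status of the rate it adds: "The 40% percentage dropout rate represents the worst-case scenario".

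The Data analysis section returns to the same minimum: "with a sample of at least 74 participants, the trial will be powered to identify at least a medium effect size". That section plans separate analyses of an intention-to-treat set, with last observation carried forward, and of completers.

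The Background gives another attrition figure, from a different source: "most studies report up to a 50% dropout rate in the use of existing mHealth and eHealth applications".

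**The concern.** The only purpose of the step from 74 to 104 is to have 74 left once dropout has occurred. Adding 40% to the target does not do that, because the loss applies to everyone randomised and not only to the original 74. If the step is wrong, a trial that meets exactly the attrition it planned for ends below the number that the article ties to its power claim. The article itself expects high attrition in this field, so this allowance is a working part of the justification of the trial's size.

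**Working it through.** **Inputs**, all from the Sample size section: required number 74 (37 per arm); dropout 40%; number to randomise 104 (52 per arm). Allocation is 1:1 (Randomization and blinding). The 74 is taken as given in steps 1 to 4.

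1. *Reproducing the stated figure.* n × (1 + dropout): 74 × 1.40 = 103.6, rounded to 104; per arm 37 × 1.40 = 51.8, rounded to 52. Both stated figures are matched exactly.
2. *The inflation that keeps 74.* n / (1 − dropout): 74 / 0.60 = 123.3, or 124; per arm 37 / 0.60 = 61.7, or 62. Check: 124 × 0.60 = 74.4. This is 124 − 104 = 20 more than stated.
3. *What 104 leaves at 40% dropout.* 104 × 0.60 = 62.4, about 62; per arm 52 × 0.60 = 31.2, about 31. The shortfall is 74 − 62 = 12, or 16% of 74. (This total of 62 completers should not be confused with the 62 per arm to randomise in step 2.)
4. *Dropout that 104 can absorb.* 1 − 74/104 = 0.288, or 28.8%.
5. *Effect on power.* The article does not name the test, its sidedness or a within-person correlation, so two bases are shown. They must not be mixed.

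| Basis | 74 retained | 62 retained |
|---|---|---|
| 74 taken as giving 80% (normal approximation) | 80% | about 73% |
| Two-sided two-sample t test, d = 0.50, alpha 0.05 | 56% | 49% |

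First row: two-sided 5% and 80% power imply a noncentrality of 1.96 + 0.84 = 2.80. Scaled to 62 it is 2.80 × √(62/74) = 2.56, and Φ(2.56 − 1.96) = 0.73. Second row: noncentral t with 37 and 31 per arm gives 0.564 and 0.491. The one-sided equivalents are 69% and 62%.

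6. *The 74 itself.* For d = 0.50 and 80% power, a two-sample t test needs 64 per arm two-sided or 51 per arm one-sided, so 74 does not come from that test. A repeated-measures between-group calculation with f = 0.25 and three time points gives 74 if the correlation is assumed to be about 0.35; it gives 62 at a correlation of 0.2 and 86 at 0.5. The article states no correlation.

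**The case against.** The arithmetic in steps 1 to 4 is not open to dispute, and nothing elsewhere in the article corrects it. Four stronger readings are tempting, and the article does not support them.

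- *That the error takes power from 80% to 49%.* A reader who sets the t-test figure beside the claimed 80% might infer this. Under that same test the full 74 gives only 56%. The inflation error accounts for 56% to 49% on that basis, or about 80% to 73% if 74 is taken as giving 80%. For the same reason, randomising 124 would not bring a two-sided t test to 80%.
- *That the power sentence in the Data analysis section is false.* It is conditional on at least 74 participants and mentions neither 104 nor dropout. The inflation error does not falsify it.
- *That there is no protection against dropout.* There is, up to 28.8%.
- *That the 50% in the Background contradicts the 40%.* The Background speaks of dropout in the use of existing apps and cites a different source; the 40% is a planning rate for this trial. The article also argues that gamification should reduce attrition. At most, the label given to the 40% is loose.

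The best defence is that the intention-to-treat analysis would include all 104, so 62 is only the completer count. The description of 62 is right. Leaving the intervention also need not mean losing all outcome data: most questionnaires are completed on the study website, and a participant assessed post intervention but lost by follow-up still contributes real data. This does not rescue the 104, however. If dropouts counted in full, no inflation from 74 would be needed; by inflating, the article treats them as lost. A separate completer analysis is also planned. For someone who leaves before the post-intervention assessment, the carried-forward value is the baseline, which supplies no observed outcome under treatment.

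**Conclusion.** Wrong as written. At the article's own 40% dropout, 104 randomised leaves about 62 completers (31 per arm), 12 fewer than the 74 it requires. Retaining 74 would need 124 (62 per arm), and 104 is enough only up to 28.8% dropout. These headcounts do not depend on the statistical test. They rest on taking 74 as the requirement and on reading the 40% as participants lost to the completer analysis. The power consequence is moderate on either basis (about 80% to 73%, or 56% to 49%) and cannot be fixed more exactly until the test behind the 74 is stated.

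**What to change.** In the Sample size section, withdraw the statement that 104 suffices at 40% dropout and replace it with wording such as: *104 randomised retains 74 completers only if dropout does not exceed 28.8%; at 40% dropout about 62 complete, and retaining 74 would need 124.*

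If a power figure is added, name the test and use one basis throughout. State the test and assumptions (sidedness, correlation) that give 74, because a two-sample t test does not.

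Optionally, soften the description of 40% as the worst case, or explain how it relates to the figure of up to 50% for app use in the Background.

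The cost is wording only. No extra enrolment is required; the one downside is a less favourable stated figure.

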#### Randomization and blinding

Selected participants will be randomized in the intervention and control trial arms in a 1:1 ratio (Fig. 5). An independent researcher will handle the randomization and the random sequence will be generated using a 1:1 allocation ratio via an online available random number generator (i.e., https://www.random.org/). More specifically, randomization will be prestratified by gender and follow a permuted-block randomization scheme to ensure a balance between the arms of the trial.

**Fig. 5 Fig5:**
[figure not shown]
Self-help, Integrated, and Gamified Mobile-phone Application (SIGMA) study flow diagram

The randomization sequence will be concealed from the staff responsible with enrolling and assigning the participants in the trial arms. This objective will be achieved by using sealed envelopes that will be numbered in advance and opened sequentially only after the participant’s name will be written on the envelope. Similarly, the personnel responsible for analyzing the data will be blinded to participant allocation.

In addition, participants will be blinded to the nature of the group to which they will be assigned, but they will be informed that they have a 1 in 2 chance of being assigned to the placebo group. Given that we use an attention placebo control group that mimics the SIGMA intervention, we are confident in a successful blinding process of the participants.

### Outcome measures and evaluation instruments used outside the application

The evaluation of the primary and secondary outcomes will be conducted before the intervention (T0), at post intervention (T1 – after 2 months), and at follow-up (T2 – after 3 months of follow-up). There will also be a constant monitoring of some of the parameters, which will be described in detail below. Most self-reported measurements, except for weight and BMI, will be recorded through the study’s website to ease visibility of multi-item questionnaires. The remaining variables, such as daily steps, attention bias, and all the constantly monitored aspects, are embedded within the mobile platform. Screening and collection of demographic data will be performed during a face-to-face meeting.

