**Methods/design:**

The efficacy of the SIGMA mHealth intervention will be investigated within a randomized, placebo-controlled trial. The intervention will be set to last 2 months with a 3-month follow-up. Selected participants will be young overweight adults with non-clinical maladaptive eating habits embodied by food cravings, binge eating, and emotional eating. The primary outcomes will be represented by changes in (1) self-reported maladaptive thoughts related to eating and body weight, (2) self-reported maladaptive eating behaviors in the range of urgent food cravings, emotional eating or binge eating, (3) as well as biased attentional processing of food items as indexed by reaction times. Secondary outcomes will be represented by changes in weight, Body Mass Index, general mood, and physical activity as indexed by the number of steps per day.

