#### Secondary outcomes

Levels of depression, anxiety, and stress will be evaluated with the Depression, Anxiety, and Stress Scales (DASS; [56]). DASS is a set of three self-report scales designed to measure the negative emotional states of depression, anxiety, and stress and has good psychometric properties (Cronbach’s alpha = 0.96; 0.89; 0.93 for the depression, anxiety, and stress scales, respectively).

The general mood will be evaluated with the Positive and Negative Affect Schedule – Short Form (PANAS-SF; [57]). PANAS has two mood subscales, the positive affect subscale, and the negative affect subscale and has good psychometric properties (Cronbach’s alpha = 0.86 to 0.90).

Weight (kg) and BMI (kg/m^2^) measures will be self-reported via the SIGMA application. Furthermore, physical activity will be assessed via the SIGMA app’s incorporated pedometer and a mean daily step count will be extracted for baseline, post intervention, and follow-up.

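### Attention bias, weight, BMI and steps are collected through the app that is itself the intervention, so stopping the app makes these outcomes more likely to be missing

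*Protocol article*

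**What the plan says.** The section on outcome measures and evaluation instruments splits data capture between two channels.

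- **Website:** "Most self-reported measurements, except for weight and BMI, will be recorded through the study’s website". This covers the multi-item questionnaires.
- **App:** "The remaining variables, such as daily steps, attention bias, and all the constantly monitored aspects, are embedded within the mobile platform".

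The Secondary outcomes section confirms the app route for weight and BMI, where "measures will be self-reported via the SIGMA application", and for the pedometer, from which "a mean daily step count will be extracted for baseline, post intervention, and follow-up". The abstract lists attention bias among the primary outcomes: "as well as biased attentional processing of food items as indexed by reaction times". The only face-to-face contact described is screening, which also records weight and BMI at entry.

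The trial has a "2-week calibration point followed by a 2-month intervention and a 3-month follow-up", so T2 falls three months after the intervention ends. The Sample size section enlarges the trial on this basis: "Assuming that up to 40% of participants will drop out of the intervention". The Background cites up to 50% dropout in the use of such apps. On analysis, "The intent-to-treat principle will be employed", with LOCF for missing values and a separate completer analysis.

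**The concern.** The measuring channel and the treatment are the same object. Someone who loses interest in the app stops the intervention and, by the same act, leaves the place where attention bias, weight, BMI and steps are recorded. An intention-to-treat comparison needs outcomes from exactly these people.

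The loss may also differ by arm. The control app has every module except the game. The Background and Discussion present gamification as a way to improve adherence and reduce attrition. If that is right, more SIGMA participants will still be in the app at T1 and T2, and the outcomes will be more complete in that arm. Neither planned analysis removes this. LOCF fills the gap with an earlier value, and the completer analysis selects on retention.

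At stake are one of the primary outcomes and the weight and activity outcomes. The beliefs, eating-behaviour, craving and binge-eating questionnaires go through the website and do not depend on app use.

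**Working it through.** **1. Capture route for each outcome, from the text**

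| Outcome | Status | Route at T1 and T2 |
|---|---|---|
| EDBQ, DEBQ, craving questionnaires, BES | primary | website |
| Attention bias (dot-probe) | primary | app |
| Weight, BMI | secondary | app; expressly excepted from the website |
| Daily steps | secondary | app pedometer |
| DASS, PANAS | secondary | website |

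For the app rows this is a stated rule, not a detail left out of a condensed article.

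**2. The plan's own figures**

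Inputs (Sample size section): d = 0.50, p ≤ 0.05, 80% power, 37 per arm, 40% dropout, 52 per arm. The 104 equals 74 × 1.4 = 103.6, rounded up. The 37 per arm does not follow from the stated inputs: a two-sided two-sample t-test needs 64. That is a separate issue and this point does not rest on it.

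**3. Upper bound on lost information**

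Observed per arm = 52 × (1 − proportion giving no app value). Power is for a two-sided two-sample t-test at 0.05, with noncentrality d × √(n/2) and 2n − 2 degrees of freedom.

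- All observed: n = 52; 0.50 × √26 = 2.55; power 0.71.
- All 40% lost: 52 × 0.60 = 31.2; with n = 31, 0.50 × √15.5 = 1.97; power 0.49.

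About 62 of 104 would then be observed, fewer than the 74 the plan says it needs. If other proportions gave no app value:

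| No app value | Observed per arm | Power |
|---|---|---|
| 20% | 41.6 | 0.62 |
| 30% | 36.4 | 0.56 |
| 40% | 31.2 | 0.49 |
| 50% (Background figure for app use) | 26 | 0.42 |

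**4. Illustration of bias from unequal retention**

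Assume no true difference, the same improvement c in everyone, and a value carried forward from baseline (change of zero) for those who stop. With retention r, the mean change in an arm under LOCF is r × c. The false difference is therefore (r for SIGMA − r for control) × c.

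- c = 0.5 SD, retention 70% versus 50%: 0.35 − 0.25 = 0.10 SD.
- c = 0.5 SD, retention 75% versus 45%: 0.375 − 0.225 = 0.15 SD.

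Both favour SIGMA, and both average to the plan's 40% loss across arms. The arm-specific retention and c are assumptions; the documents give neither. A common improvement is most plausible for weight, because both arms are asked to follow a calorie-restrictive diet.

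**The case against.** A reader might infer that post-intervention and follow-up values will exist only for current users. The article does not say that. Being embedded in the app tells us where the task sits, not who is asked to do it. The same section says that primary and secondary outcomes will be evaluated at T0, T1 and T2, with no exception for those who stop. The dot-probe is a discrete task and weight a single entry, so someone who has stopped playing could reopen the app once for both. Reminder procedures are also commonly left to a full protocol, and the schedule figure is not available here. This stands: the route makes loss more likely, not certain. Steps are the exception, because they need the app to be running.

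A reader might also take 49% against 71% as the expected loss of power. It is not. The 49% assumes that everyone who stops gives no app value, and the 71% assumes nobody is missing, which a website form would not achieve either. A t-test also stands in for the planned mixed model.

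Nor can one say that LOCF will shrink a true effect to 60% of its size. That assumes people who stop would have had the full effect. If they gain less, the true intention-to-treat difference is itself smaller.

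Unequal retention is plausible on the plan's own rationale but not established, since self-monitoring and the pedometer are in both apps. The choice of LOCF is a wider issue that also affects website outcomes when they are missing.

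What survives is that weight and BMI are deliberately kept off a channel that already exists and does not depend on using the intervention, and that the article does not say the T1 and T2 dot-probe is sought from people who have stopped.

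**Conclusion.** The concern holds in limited form. Attention bias, weight, BMI and steps have no stated route outside the app at T1 or T2, and the plan expects up to 40% to leave the app. Missing data on these outcomes will therefore tend to follow adherence, possibly more in the control arm, and LOCF does not correct for this. The questionnaire-based primary outcomes are not tied to the app.

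The power figures in the working bound the loss of information and do not predict it. The 0.10 SD false difference shows how the bias would arise under assumed retention and a common improvement; it is not an estimate. The change is worth making because it is nearly free and because values not collected at T1 and T2 cannot be recovered later.

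**What to change.** - **Weight and BMI:** collect weight at T0, T1 and T2 on the study website, with the questionnaires, for every randomised participant whether or not they still use the app. Derive BMI from it.
- **Attention bias:** state that the T1 and T2 dot-probe is requested from all randomised participants, including those who have stopped, through a one-off prompt to open the app for that task.
- **Steps:** keep as an app outcome, and report the number contributing in each arm at each time point.
- **Wording:** the section heading describes instruments used outside the application, while its text places several inside it. Reconcile the two.

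The cost is one extra form entry, which current app users would make separately at each assessment, and reminder messages. The intervention, randomisation and assessment times stay as they are.
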